### GP recruitment and patient enrolment

GPs are eligible to participate in the trial if they provide in their practice standard care as opposed to exclusively providing alternative medicine such as acupuncture or homeopathy. Participating GPs must sign an informed consent form and agree to implement the study protocol. Potentially eligible GPs are identified via the Regional Primary Care Physician Association with an address database.

In both groups, GPs identify eligible CHF patients and ask them to participate. The GPs recruit the first eligible patients to participate in the clinical trial until they have included at least five patients. The inclusion period lasts one year. The GPs in the two groups receive the same compensation for their participation. The GP shares an information sheet and a consent form with the patients. During the inclusion visit, the GP explains the aim of the clinical trial, i.e. understand and improve treatment of patients with heart failure, without describing the objectives. Patients willing to participate sign the consent form at home within seven days of the visit and send it to the data management centre with the first two quality of life questionnaires.

### Intervention group

No medication is tested in this trial and the GPs are allowed to adapt patients’ treatment if necessary. The complex intervention consists of training at the GP practice with an interactive 2-day workshop to provide a patient’s education programme.

#### GP training

At an interactive 2-day workshop, GPs assigned to the intervention group are trained to perform case management and educate patients (Table 1). The two-day workshop includes the following elements: information on the case report forms and the patients’ inclusion/exclusion criteria, information on CHF (epidemiology, NYHA stages, treatment, patient adherence etc.) based on The European Society of Cardiology guidelines [5], information on patient education concepts, principles of GP-patient-communication, lifestyle counselling and motivational interviewing based on the 5As model (ask, assess, advise, assist and arrange) [20] and the use of several case vignettes simulating GP- patient consultations. GPs are trained to educate patients on the main topics of clinical alarm signs, physical activity, diet and cardiovascular risk factors. During the 2-day workshop, GPs are trained by experts: a nutritionist, an endocrinologist, a cardiologist, three GPs and a pharmacist, who are all patient education trainers and one has a Masters degree in patient education.

**Table 1 Tab1:** **Training seminar for general practitioners: 2-day workshop**

Module 1: Introduction	- Introduction to the concepts of the ETIC trial and patient education
Module 2: Heart failure	- Chronic heart failure: definitions; epidemiology; clinical diagnosis; treatment guidelines∗; echocardiographic criteria; cardiac biomarkers: B-type natriuretic peptide (BNP) and NT-proBNP (how, when to prescribe them, how to use them)
	- Clinical symptoms: how to recognize heart failure in daily practice?
	- NYHA stages: definitions, assessment of NYHA stages from case vignettes
	- Suspicious clinical signs
	- Adaptation of physical activity as a function of the NYHA stage
Module 3: Concepts of patient education	- Assessment and building on the patient’s previous knowledge
	- Identification of life-style and dietary habits, physical activity, hobbies, leisure activities, projects, and resources available to the patient
	- Assessment of the patient’s stage of change, motivation and attitudes
	- Collaboration with the patient to define achievable and measurable objectives
Module 4: Communication	- Communication skills
	- Communication tools
	- Motivational interviewing
	- Lifestyle counselling based on the 5As model (ask, assess, advise, assist, and arrange)
Module 5: Role-playing to simulate a patient consultation with the general practitioner	- Identification and use of the patient’s knowledge (clinical alarm signs, physical activity, diet and cardiovascular risk factors), values, motivation, projects and resources to implicate the patient in their personal objectives
	- Classification of the personal objectives by therapeutic priority and patient preference
	- Use of effective communication strategies
Module 6: Case report forms	- Inclusion and exclusion criteria
	- How to promote and present the ETIC trial to patients
	- How to fill in the case report forms
	- How to organize the follow-up and topics: educational booklet and educational tools (i.e. dietary leaflets, clinical alarm signs)

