Therefore we want to assess the effectiveness of a complex intervention that incorporates education of patients with CHF by GP’s trained to promote self-care management and behaviour management. The aim of the ETIC trial (Education Thérapeutique des patients Insuffisants Cardiaques/Therapeutic Education for patients with Cardiac Failure) is to improve the quality of life of patients with heart failure though a complex intervention involving patient and GP education in primary care. The secondary objectives are to assess the effects of the training on: all-cause and heart-failure (HF)-associated mortality; all-cause and HF-associated hospitalisation; the cumulative number of all cause death and HF hospitalisations; adherence to treatment; changes in NYHA heart failure stage; changes weight and body mass index (BMI) and treatment for a follow-up period of 19 months.

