### Instruments and outcomes

The primary outcome is the patients’ quality of life as measured by SF-36 [16] and the Minnesota Living with Heart Failure Questionnaire (MLHFQ) [17]. The SF-36 is a generic measure of health impairment, with scores ranging from 0 to 100: zero indicates the worst quality of life and 100 the best. The MLHFQ is specific for chronic heart failure and has 21 questions with scores ranging from 0 to 105: zero indicates best quality of life and 105 the worst. Quality of life is assessed at baseline and at 7, 13 and 19 months by the patients, or their main caregiver, within 7 days of their appointment with their GP. A score of < 24 on the MLHFQ signifies a good quality of life, a score between 24 and 45 signifies a moderate quality of life, and a score > 45 signifies a poor quality of life [18]. We will assess these cut-off scores to interpret results in clinical terms. We were unable to find published cut-off information for the SF-36 health scores.

The secondary outcomes are: all-cause and heart-failure-associated mortality; all-cause and heart-failure-associated hospitalization, number of days in hospital; the cumulative number of all cause death or HF hospitalizations and the cumulative number of days of hospitalisation; adherence with therapy; evolution of NYHA heart failure stage; evolution of treatment; and changes in weight and body mass index (BMI) at 19 months. We will assess guideline adherence of treatment at baseline and during the follow-up period. Patient adherence with therapy will be assessed by the patients themselves with a self-administrated questionnaire (validated in French) at baseline and at the end of follow-up period [19].

Should the planned follow-up appointment be missed, the reason is identified and categorised as follows: lost-to-follow-up; death; unable to attend for another reason. Hospitalisations and mortality will be recorded by GPs at each planned visiting case report form.

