**Table 2 Tab2:** **Education intervention topics**

**Knowledge, attitudes and motivation**	- Do you suffer from heart failure?
	- What is « heart failure » for you?
	- What do you know about heart failure?
	- How do you live with this disease?
	- What impact heart failure has on your life (personal, professional, social)?
	- What are your fears?
	-What are your expectations?
**Clinical alarm signs**	- For you, what could be a clinical alarm sign of your heart failure?
	- What should you do to detect clinical alarm signs?
	- Do you know what to do if you detect clinical alarm signs?
**Physical activity**	- What does physical activity mean for you?
	- What is yours? Household?, leisure (e.g. gardening)? Transportation (e.g. walking, car)?
	- When are you breathless? (NYHA)?
	- What would you be ready to change in your habits?
**Diet**	- Where do you eat yours meals?
	- Who does the cooking?
	- High salt food: what do you know about? What is your comsumption? What is your point of view, what changes are you ready to start?
	- BMI ≥ 30 : diet mistakes (snack food, overeating) or diet troubles ?
	- BMI ≤ 18 adult patients or 21 ealderly patients : diet mistakes or diet troubles ?

There is no predetermined order, each theme is evoked depending on the patients’ needs and based on the first education session (Additional file 2).

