### Control group

The GPs in the control group attend a three-hour information evening session to learn about the case report forms and the patients’ inclusion/exclusion criteria. Their patients have the same schedule for visits as those in the intervention group (at 1, 4, 7, 10, 13, 19 months) but without specific education intervention.

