#### Statistical analysis

The statistician will be blinded with regard to treatment allocation. The responses to the questionnaire will be entered into a customised Access database (Microsoft, Redmond, Wash, US). Analyses will be made using Stata, version 13 (StataCorp, College Station, Tex, US). If necessary, an adjustment to accommodate differences between the baseline characteristics of the groups will be made. Continuous data will be presented as mean ± standard deviation (SD). The comparisons between study groups will be analysed using Chi-square or Fisher's exact test for categorical variables, and Student's or Mann–Whitney tests for quantitative variables, with normality verified by the Shapiro-Wilk test and homoscedasticity by the Fisher-Snedecor test. The correlation between SF-36 and MLHFQ will be assessed using Pearson’s correlation coefficient. Hierarchical linear regression models with random-effects levels for practice, individuals within practices and repeated measurements per individual (slope and intercept) will be used to estimate the effects of the intervention on SF-36 and MLHFQ scores for the post-baseline time points. These models will include an interaction factor between both the randomisation group and the particular time point, and will be adjusted for baseline SF-36 scores, age, gender, diagnosis, smoking history, treatment and socioeconomic status. Intra-class correlation coefficients will be presented by group. The secondary analyses will compare deaths (overall and due to heart failure) using Kaplan-Meier estimation and the Cox proportional-hazards regression model, hospitalisations (overall and due to heart failure), NYHA stage, treatment, adherence, weight and obesity between the groups with longitudinal random-effects models described previously. Estimation methods developed by Verbeke and Molenberghs will be used to account for missing data (GPs and patients) [25].

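### NYHA staging practice is described for intervention GPs only, so a between-arm difference in NYHA evolution cannot be cleanly separated from a difference in measurement

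*Protocol article*

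**What the plan says.** The Background section names "changes in NYHA heart failure stage" among the secondary objectives. Instruments and outcomes lists "evolution of NYHA heart failure stage" as a secondary outcome. Statistical analysis says the trial will compare "NYHA stage, treatment, adherence, weight and obesity between the groups with longitudinal random-effects models described previously".

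The two arms' GPs are prepared differently. Under GP training, "GPs assigned to the intervention group are trained to perform case management and educate patients" at a two-day workshop, and Module 2 of Table 1 includes "NYHA stages: definitions, assessment of NYHA stages from case vignettes". Under Control group, the GPs "attend a three-hour information evening session to learn about the case report forms" and the inclusion and exclusion criteria. Visits follow the same schedule in both arms.

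NYHA stage also decides entry: stages I to III are eligible and stage IV is excluded. GPs in both arms identify the eligible patients.

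**The concern.** NYHA class is a clinician's judgement about symptoms, so it depends on how the rater applies the definitions. If one arm's raters have practised staging on vignettes and the other arm's have not, the intervention may change how the outcome is measured as well as the outcome itself. Sharper recognition of limitation would make the intervention arm look worse, and fewer false attributions of limitation would make it look better. The raters would also know which arm they are in. What is at stake is whether a difference in NYHA evolution can be read as an effect on patients.

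**Working it through.** The article gives no figure on NYHA rating, so there is none to reproduce. The check compares the passages and then uses a short illustration with assumed values.

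**1. Is staging taught in one arm only?** The GP training section lists the case report forms and eligibility criteria as one item of the workshop, and information on heart failure, including NYHA stages, as another. The Control group section lists only the first. As described, staging content is separate from form and eligibility training and appears in one arm.

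**2. Who rates?** Not stated for NYHA. GPs run the visits, select the patients, and record hospitalisations and deaths on the case report form. No independent or blinded NYHA assessor is described. That the GP rates is a strong inference, and so is the GP's knowledge of allocation, because the GP either attends the workshop and delivers the education or does not.

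**3. When does training occur?** The Discussion says GPs were randomised before patients were included. Module 6 of Table 1 covers eligibility and how to present the trial to patients. The workshop therefore appears to precede the baseline rating.

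**4. Is it acknowledged?** The limitations in the Discussion cover possible recruitment of sicker patients by trained GPs, volunteer GPs, the Hawthorne effect and low power for secondary outcomes. Unequal NYHA rating is not among them.

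**5. Effect at a single visit.** Assumed, not from the documents: the true share in stage III is p = 0.30 in both arms. Observed share = p × Se + (1 − p) × (1 − Sp).

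| Assumption (intervention vs control) | Intervention | Control | Difference |
|---|---|---|---|
| Se 0.90, Sp 0.90 in both | 0.270 + 0.070 = 0.340 | 0.340 | 0 |
| Se 0.95 vs 0.85; Sp 0.90 | 0.285 + 0.070 = 0.355 | 0.255 + 0.070 = 0.325 | +3 points |
| Sp 0.95 vs 0.85; Se 0.90 | 0.270 + 0.035 = 0.305 | 0.270 + 0.105 = 0.375 | −7 points |
| Se 0.95, Sp 0.95 vs Se 0.80, Sp 0.90 | 0.285 + 0.035 = 0.320 | 0.240 + 0.070 = 0.310 | +1 point |

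The artefact can go either way, and its size is not proportional to the gap in accuracy.

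**6. Effect on change from baseline.** If Se and Sp are constant over time within an arm, the observed change in share is (Se + Sp − 1) × Δ, where Δ is the true change.
- Rows 2 and 3: 0.95 + 0.90 − 1 = 0.85 in the intervention arm and 0.85 + 0.90 − 1 = 0.75 in the control arm. The same Δ appears as 0.85Δ and 0.75Δ, a gap of 0.10Δ.
- Row 4: 0.95 + 0.95 − 1 = 0.90 against 0.80 + 0.90 − 1 = 0.70, a gap of 0.20Δ.
- If Δ = 0, the gap in net change is zero.

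**7. Why cancellation is incomplete.** Step 6 ignores selection at entry. A patient truly in stage IV but rated III is admitted, and may later be rated IV and appear to worsen. A patient truly in stage III but rated IV is not admitted, so the opposite error is not there to balance it. This will be commoner where rating is less accurate. Random misclassification also affects how many patients appear to change stage in either direction, even when net change is zero. The document gives nothing from which to size either effect.

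**The case against.** **Timing.** The strongest objection is that the same GP, already trained, rates the patient at baseline and at follow-up, so a constant shift drops out of change. This stands in part: it removes most of a simple shift, but not unequal misclassification on a coarse ordinal scale cut at entry.

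The timing also rules out a tempting inference. A reader might suppose that if training led GPs to restage 10% to 20% of patients, the arms would differ by 10 to 20 points in the proportion changing stage, or 16 to 32 of 160 patients per arm (200 less 20% dropout). That would need the training to fall between baseline and follow-up, which the document does not support.

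**Control content and rater.** The control session is condensed to one sentence. It covers eligibility criteria that are themselves framed in NYHA stages, so control GPs may hear the definitions. The rater is inferred. Both caveats stand, and what remains is that staging practice is described in one arm only.

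**Drift.** A reader might infer that the NYHA-tagged breathlessness question in Table 2 shifts ratings over follow-up in the intervention arm. It is an education prompt under physical activity. The note to the table says topics have no fixed order and follow the patient's needs, and nothing says it is asked at every visit or used for staging. Drift is speculative.

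**Eligibility.** The Discussion already says that trained GPs may include more severely ill patients, and it plans adjustment for differences between groups. That part is largely disclosed; unequal rating of the outcome is not.

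**Conclusion.** The point holds as a limit on interpreting one secondary outcome. Staging practice is described for one arm's apparent raters and not for the other's, no independent assessor is described, and the limitations do not mention it. An observed difference in NYHA evolution therefore cannot be cleanly separated from a measurement difference of unknown size and direction.

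The +3, −7 and +1 point figures rest on an assumed 30% stage III share and assumed accuracies, and they apply to one visit. In net change the same assumptions leave 0.10 to 0.20 of the true change, plus an unquantified part from the entry cut. The conclusion also assumes that the GP is the rater and that control GPs had no staging practice.

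A reader might go further and conclude that the trial cannot answer the NYHA objective at all, or that a difference would be wholly artefact. The document does not support that, since part of the bias cancels and its size is unknown. The primary outcome, completed by patients or their main caregiver, is not directly affected.

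**What to change.** Give GPs in both arms the same NYHA definitions and the same staging vignettes, or a common staging aid in the case report form, before they rate any patient at baseline. Limit this to measurement content, with no education or counselling material.

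Trial status says the study is ongoing, so some baseline ratings may already exist. For patients whose baseline rating was made without the common material, do not introduce it during follow-up: the rater's calibration would change between baseline and follow-up, creating the very artefact to be avoided. Report their NYHA evolution descriptively and draw no efficacy conclusion from it.

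Add to the limitations that NYHA rating was unblinded and that preparation for it was unequal. Common material would not remove the influence of knowing the allocation, so the unblinded part of that statement is needed in any case.

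The cost is a handout or a page in the case report form and some minutes of the existing three-hour control session. The downsides are small: control GPs receive a little of the workshop's staging content, and the NYHA result carries a weaker claim.

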#### Patient’s intervention level

The patients’ education sessions will be performed by their own GPs. The education sessions are standardised both in their timing, every three months (Figure 1), and topics covered (Table 2). GPs have an education booklet in their case report form with the topics covered and education tools (ie dietary leaflets, clinical alarm signs) (Additional file 1). The first educational session (educational diagnosis) for the patient occurs at month one (Figure 1) and covers several topics: life-style and dietary habits, physical activity, hobbies, leisure activities, projects and details resources available for patients (Additional file 2). This first step is necessary to establish existing knowledge, attitudes and motivation. Patients have four further education sessions at 4, 7, 10 and 13 months followed by an overview session six months after the last education session at month 19.

**Table 2 Tab2:** **Education intervention topics**

**Knowledge, attitudes and motivation**	- Do you suffer from heart failure?
	- What is « heart failure » for you?
	- What do you know about heart failure?
	- How do you live with this disease?
	- What impact heart failure has on your life (personal, professional, social)?
	- What are your fears?
	-What are your expectations?
**Clinical alarm signs**	- For you, what could be a clinical alarm sign of your heart failure?
	- What should you do to detect clinical alarm signs?
	- Do you know what to do if you detect clinical alarm signs?
**Physical activity**	- What does physical activity mean for you?
	- What is yours? Household?, leisure (e.g. gardening)? Transportation (e.g. walking, car)?
	- When are you breathless? (NYHA)?
	- What would you be ready to change in your habits?
**Diet**	- Where do you eat yours meals?
	- Who does the cooking?
	- High salt food: what do you know about? What is your comsumption? What is your point of view, what changes are you ready to start?
	- BMI ≥ 30 : diet mistakes (snack food, overeating) or diet troubles ?
	- BMI ≤ 18 adult patients or 21 ealderly patients : diet mistakes or diet troubles ?

There is no predetermined order, each theme is evoked depending on the patients’ needs and based on the first education session (Additional file 2).

Patient education sessions (at 4, 7, 10, 13, 19 months) are based on patient’s experience and knowledge of their illness, including clinical alarm signs, physical activity, diet and cardiovascular risk factors. Patient education sessions are adapted for each patient, based on the first education session, one month after inclusion and at each of the following visits to match the needs and motivation of each patient. As this is a pragmatic trial aiming to assess the impact of an educational programme in daily clinical practice, the delivery of the program is allowed to vary between health care providers. The health care providers have the flexibility to adapt the programme according to patients’ needs. For example, if a patient smokes but does not want to discuss this, this is respected but, at the following visit, the patient is asked again if they want to discuss their smoking habits [21]. After each education session, GPs write in their case report form which topics they explored (Additional file 3). At the end of each visit, patients fix their own personal objectives with the GP, for example, only eat cooked pork meat products twice a week, verify weight once a week and walk their dog once a week (Additional file 3). These objectives are evaluated at the following patient education session and can be modified and adapted at each visit. This continuous evaluation of patients’ needs and objectives provides the basis for further education sessions. The GPs are trained to manage their own education objectives (i.e. HTA, diet, adherence, etc.) and patient objectives (i.e. to be able to walk their grandchildren to school). They simulate several patient education sessions during the 2-day workshop. GPs have case report forms with written standardised instructions for the programme patient education sessions and to summarise each consultation and write personal patient objectives.

